**Fig. 1 Fig1:**
[figure not shown]
Flow of participants

#### Inclusion criteria

The intent of this study is to target persons with high risk for developing CRPS. Therefore, it is limited to women with fragility or low-impact type fractures who are:55 years or oldermanaged with closed orthopaedic treatment and cast immobilizationreporting a numerical pain rating of greater than 3/10 within 1 week of initial medical management of their fracture

These patient factors are known to have strong associations with type I CRPS development [4, 26, 34].

#### Exclusion criteria

The following factors will indicate exclusion from the present study:Concurrent rehabilitation services elsewhere (chiropractic, acupuncture, occupational or physical therapy) that address sequelae of forearm fractureSurgical fixation of DRFCentral nervous system disorders (e.g., Brain injury, Spinal Cord Injury, Parkinson’s Disease, Multiple Sclerosis)Concomitant ipsilateral injuries such as both bone forearm fracturesOther injuries to the affected limb interfering with baseline affected limb functionCognitive disorders which would preclude the participant from following the testing commands and home program participationDiagnosis of dyslexia as this may impact the laterality component of mGMIConditions of the contralateral upper limb which would result in painful and markedly limited active hand, wrist and forearm motion as this may impact the brain’s ability to perceive safe and proficient movement during mirror therapyVisual impairments resulting in the inability to participate in mGMI components

### Intervention procedures

DRF will be managed as per the American Academy of Orthopedic Surgeons guidelines [13]. Upon enrollment in the study, participants will be randomized to an mGMI +SOC group or a SOC only group. The SOC group includes a combination of clinic and home based programming to address hand, elbow and shoulder motion as well as edema control whereas the mGMI +SOC group receives the same SOC programming in addition to MRT interventions intended to maintain the affected limb’s cortical representation. Participants in both groups will complete four clinic-based intervention sessions of an hour each across a 6 week period where thefocus will be on facilitating home program competency and advancement as indicated. The first session will occur within one week of cast treatment and home programming will supplement these clinical sessions. The entire therapy protocol for each group is standardized and manualized to ensure intervention fidelity. SOC and all phases of mGMI home programming are standardized and are to be provided in the form of written materials. The format will be one on one with the interventionist and will involve instruction in home programming as described below. All interventions will be carried out by certified OTs, including a certified hand therapist. Table 1 illustrates the intervention timeline. To enhance intervention fidelity both interventions are protocolized and manualized and the evaluator all interventionists will undergo formal training by the PI. Prior to the initiation of the trial, the PI will conduct a competency assessement of the evaluator and the interventionists.

#### Home program (mGMI + SOC or SOC)

SOC consists of the aforementioned 4 one-on-one treatment sessions and a home exercise program [50, 51]. Participants will be instructed to complete their home program three times daily for 15 min. This will consist of AROM for 10 repetitions each of thumb opposition, thumb radial abduction and extension, finger metacarpophalangeal joint flexion with interphalangeal joint extension, tendon gliding series, finger abduction and adduction, forearm supination and pronation, elbow flexion in supination alternating with elbow extension in pronation, “shoulder rolls” for scapular active motion, shoulder flexion to 90 degrees, shoulder internal rotation behind the back with a light dowel, shoulder external rotation with the elbow at 90 degrees and forearm sliding on a table, shoulder abduction with the forearm sliding on a table, and supine shoulder flexion with the dowel. Exercises should be completed within a pain-free arc of movement. The programs’ intensity and duration will conform to the American Academy of Sports Medicine’s guidelines for older adults [52] however will be tailored according to each participant’s unique habits and routines so as to enhance adherence.

Edema will be addressed through elevation above heart when at rest and for 10 min on the hour. When resting in a seated or supine position, participants will be instructed to use pillows to accomplish elevation and to keep elbows in an extended position. Compression will not be recommended due to the linkage between tight casting and CRPS development [18]. Instructions for elevation will be provided immediately following orthopedic intervention. Strict elevation will be recommended for the first 72 h after the injury.

#### Modified graded motor imagery (mGMI) home program

Although the GMI intervention reported by Mosely had significant functional, pain-reducing, and edema-reducing benefits, it may have limited feasibility as it requires performing a home program for 10 min each waking hour. For this reason, Lagueux et al. [53] designed and implemented a modified approach to GMI with three 10 min sessions performed daily. In a six-week program, persons with acute type 1 CRPS reported significantly less pain (*p* = 0.046) on McGill Pain Questionnaire, and improved maximum grip strength measured by dynamometry (*p* = 0.040). The present protocol is based on the modified GMI (mGMI) approach by Lagueax et al. [53] which involved four stages of: 1) Laterality, 2) Explicit motor imagery, 3) Mirror therapy with unaffected hand only and 4) Mirror therapy with bilateral hands. The present study will only involve use the first three phases, given the constraint of cast immobilization. Each phase will be one to two weeks in duration. Participants will be instructed to perform all phases of the mGMI home programming for 10 min, three times a day, six days a week, in addition to performing AROM and elevation as per the SOC. The following describes the mGMI home program of the study:

##### Phase 1 (left/right discrimination)

When presented with a stack of 50 photos of hands, wrists, and forearms in various postures and orientations (Fig. 2), the participant, without adjusting the cards’ positioning, will determine spontaneously whether it is a right or left upper limb and sort the cards into 2 separate piles. During the clinic session of week two, or when the participant is ready, they will be progressed to the next phase.

**Fig. 2 Fig2:**
[figure not shown]
Examples of photos for mGMI phases 1 and 2

##### Phase 2 (explicit motor imagery)

Twenty-five of the 50 images (those which represent the affected side) will be used. In this phase, the participant will select and view a single card and then imagine moving the hand of the casted arm into such a posture and imagine experiencing any relevant sensations including the feeling of movement. The participant will repeat the procedure with all 25 photos at least three times a session. If necessary, to meet the 10 min’ duration, the participant will view magazine photos of an individual performing an activity of meaning. Photos will be chosen that depict the distal aspect of their affected extremity. Upon returning in week four participants will progress to the next mGMI protocol phase.

##### Phase 3 (mirror therapy with mobilization of the non-affected hand)

During this phase, the participant will execute the movement depicted by the 25 cards representing the non-affected wrist. They will move the non-affected limb slowly and gently, five to 10 times, while watching the reflection in the mirror. The affected limb remains immobile, hidden in the mirror box. Therefore, the participant views the illusion of moving their injured hand and wrist (Fig. 3*).*

**Fig. 3 Fig3:**
[figure not shown]
Phase 3: Mirror Therapy

If the participant experiences an increase of more than 2/10 in pain intensity as per the NRS during the mGMI protocol, they will stop and document how long they could participate in that home program session before the increase in pain. There are two options for subsequent sessions: (a) exclude the image that caused the pain or (b) perform the exercise for recorded time minus one minute. The participant will progress to the next phase when exercises do not cause an increase in pain. The interventionist will consider each patient’s pain status prior to progressing her into each new phase. The mGMI protocol, as described above, is that of Lagueux et al. [53] and has been validated for use in persons with Type I CRPS.

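### The mGMI in-session pain stop (a rise of more than 2/10) cannot be triggered in a session started at 8, 9 or 10, and no upper pain limit is set at entry: a minor participant-protection flaw with a one-line fix

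*Protocol article*

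**What the plan says.** The pain rule stands in the Protocol article after Fig. 3, at the end of the description of Phase 3, and is worded for the whole mGMI programme: "If the participant experiences an increase of more than 2/10 in pain intensity as per the NRS during the mGMI protocol, they will stop". The participant then notes how long she lasted, and later sessions are changed in one of two ways: "exclude the image that caused the pain or (b) perform the exercise for recorded time minus one minute".

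Two further rules there govern movement between phases. One is a no-increase condition: "The participant will progress to the next phase when exercises do not cause an increase in pain". The other has the interventionist consider each patient's "pain status prior to progressing her into each new phase".

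The Inclusion criteria section requires a pain rating above 3/10 within a week of initial management and gives no upper limit. It states the aim: "The intent of this study is to target persons with high risk for developing CRPS". The list in the Exclusion criteria section, opened by "The following factors will indicate exclusion from the present study", has no entry for high pain in the affected limb.

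The planned dose is "mGMI home programming for 10 min, three times a day, six days a week".

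**The concern.** A rule based on change on a bounded scale runs out of room near the top. Here the trial selects women partly for high pain, and the only rule that stops a home session in progress needs a rise that some of them cannot register. The dose adjustment depends on that stop: without a stop there is no recorded time to shorten, and the rule does not prompt removal of an image.

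At stake is consistent protection. A woman whose pain goes from 7 to 10 is told to stop and her later sessions are modified. A woman whose pain goes from 8 to 10, or from 9 to 10, ends at the same worst score and the rule asks nothing of her. No endpoint or estimate is involved.

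**Working it through.** The plan gives no figure to reproduce here, so the check is an enumeration.

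**Inputs**
- Stop threshold: a rise strictly greater than 2 (pain rule after Fig. 3).
- Scale: 0 to 10. The rule writes the NRS as a score out of 10, and the Background section on type I CRPS and DRF names a 0-10 numerical pain scale.
- Entry pain: above 3, no ceiling (Inclusion and Exclusion criteria).
- Dose: 10 minutes, three times a day, six days a week (mGMI home program).

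**Formula.** Largest possible rise = 10 − start. The stop is reachable only if 10 − start > 2. On whole-number ratings a rise of more than 2 means at least 3, so the firing score is start + 3.

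| Start | Largest rise | Rule fires at |
|---|---|---|
| 4 | 6 | 7 |
| 5 | 5 | 8 |
| 6 | 4 | 9 |
| 7 | 3 | 10 |
| 8 | 2 | never |
| 9 | 1 | never |
| 10 | 0 | never |

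Three of the seven whole-number scores admitted at entry (4 to 10) cannot trigger the stop. Decimal ratings do not help: any start of 8.0 or more leaves a rise of at most 2.

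**Do other provisions stop a session in progress?**
- The no-increase condition acts between phases. It can still register a rise from 8 or 9. From 10 it is always satisfied, which leaves the interventionist's review.
- That review takes place before each new phase, and no pain level is given for it.
- The adherence log and medication diary are reported weekly, after the event.
- Adverse-event questions are asked at contacts; withdrawal concerns leaving the trial.
- The Movement representation techniques section makes phase transitions depend on symptoms being controlled, again between phases.

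All are real protections; none is a rule for stopping a session under way.

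**Candidate repairs**
- *A rise of 2 or more*: reachable from 8 (8 to 10), but not from 9 (largest rise 1) or 10 (largest rise 0).
- *A rise of more than 2, or any increase that reaches 10*: firing score = the smaller of start + 3 and 10, for starts up to 9. From 4, 5, 6 and 7 this gives 7, 8, 9 and 10, unchanged. From 8 and 9 it gives 10. From 10 no increase is possible, so that case needs separate handling.

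**Dose.** Planned: 3 × 10 = 30 minutes a day, and 30 × 6 = 180 minutes a week. A stopped session loses at most 10 of 180 minutes (5.6%). Under the second option the recorded time is at most 10 minutes, so the next session is at most 9, a loss of at least 1 minute in 10.

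**The case against.** The strongest reply is that this is a rule about provoked pain, not absolute pain. It adjusts the exercise when the exercise makes things worse, and severe pain that stays level is not its target. That stands, and it is why a start at 10 should not by itself cancel a session. It does not answer the rises from 8 to 10 and from 9 to 10, which are provoked pain and go undetected.

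A second reply is that the article says the therapy is manualized, and the manual may cover high starting pain. The manual is not shown, so the point concerns the rule as printed. That rule is stated in full, with threshold, action and follow-up, and it fails in part of its own range; this is different from detail left to another document. The article also says the protocol was validated in persons with type I CRPS, but that does not change the arithmetic.

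Third, the intervention is mild: card sorting, imagery, or gentle movement of the other hand. In the mirror phase, "The affected limb remains immobile, hidden in the mirror box". Nothing obliges a woman to continue a home session that hurts. This stands and sets the size of the point.

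A reader might infer that many sessions are affected, because the Background cites 81% with severe or very severe pain at initial follow-up. The documents do not support that. The figure is not an NRS distribution, and entry pain is taken once, within a week of initial management, whereas the rule applies to pain during each home session over about six weeks.

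**Conclusion.** The point holds as a minor participant-protection flaw, worth correcting because it is cheap. The in-session stop and its dose adjustment cannot be triggered from a start of 8, 9 or 10, and nothing in the entry criteria keeps such starts out. The arithmetic is exact, given a 0-10 scale and a rise measured from the level at the start of the session. The number of women or sessions affected cannot be derived from the documents.

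Two stronger readings should be resisted. One is that women in high pain are left unprotected: the phase-progression condition, interventionist review, weekly reports, adverse-event questions and withdrawal all remain, and a participant can stop by herself. The other is that the trial's results are compromised: power, error rates and conclusions do not depend on this rule.

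**What to change.** Reword the trigger to *an increase of more than 2/10, or any increase that reaches 10/10*, and keep the same two options for later sessions. This leaves the rule as it is for starts of 7 or below and extends to 8 and 9 what it already does from 7. Add that a participant whose pain is already 10/10 before a session notes this and contacts the interventionist, who decides whether she continues. Automatic deferral is not advised: it would withhold treatment from women the trial targets without evidence that the exercise provokes their pain. Record the starting NRS in the existing home log.

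The cost is one or two sentences in the protocol and manual, one extra log entry per session, and a slight loss of mGMI dose in sessions started at 8 or 9 that reach 10.

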### Outcome measurements

All outcome measures will be administered by a single licensed OT who will be blinded to allocation. Blinded assessments occur within 1 week of cast immobilization (baseline), at four three weeks post cast immbolization, cast removal, and at three months post cast removal. A list of measures and a timeline of all data collection points can be found in Table 2.

**Table 2 Tab2:** Data collection time points

		Baseline (Immediately prior to Starting Therapy)	3 weeks post casting	Week of Cast Removal	4 weeks after cast removal	12 weeks after cast removal
Primary Outcomes	McGill Pain Scale	X	X	X	X	X
	Patient Rated Wrist Evaluation			X	X	X
	Assessment of CRPS I (Budapest criteria)			X	X	X
Secondary Outcomes	Finger Edema (%Unaffected)	X (Affected and Unaffected)	X	X	X	X
	Wrist/Forearm Goniometry (%Unaffected)	X (Unaffected)		X	X	X
	Grip Strength (%Unaffected)	X (Unaffected)			X	X
	Therapy Adherence Log		X	X		
	Patient’s Global Impression of Change			X		
	Continued Hand Therapy Sessions				X	X
	Pain Medication Use	X	X	X	X	X
	Blinding Questionare			X		

#### Primary outcomes

##### PRWHE

The PRHWE [15] is a 15-item questionnaire designed to measure wrist pain and disability in activities of daily living. The PRHWE allows patients to rate their levels of wrist pain and disability from 0 to 10, and consists of 2 subscales: 1) Pain subscale: contains 5 items each of which is further rated from 1 to 10. The maximum score in this section is 50 and minimum 0; 2) Function subscale: contains total 10 items which are further divided into 2 sections i.e. specific activities (having 6 items) and usual activities (having 4 items). The maximum score in this section is 50 and minimum 0. The PRWHE is a widely-used instrument with sound psychometric properties and an established minimum clinical important difference (MCID) after DRF [15, 54, 55] of 11.5 points. The PRWHE has demonstrated higher responsiveness to change after DRF than the DASH questionnaire, as indicated by a higher standardized response mean (SRM) over three and six month periods [55].

##### McGill pain scale

The McGill Pain Scale – Short Form (SF-MPQ), a gold-standard assessment of pain-related affect and intensity [56] will be administered to assess the qualitative and quantitative aspects of pain. The pain rating index has 2 subscales: 1) Sensory subscale with 11 words, and 2) Affective subscale with 4 words from the original MPQ. These items are rated on an intensity scale as 0 = none, 1 = mild, 2 = moderate and 3 = severe. There’s also one item for present pain intensity and one item for a 10 cm visual analogue scale (VAS) for average pain.

Follow up at the mid-point of the intervention (three weeks) is warranted as significant differences in pain have been reported as early as two weeks following the initiation of GMI in persons with CRPS. Additionally, assessing pain at four and 12 weeks post cast removal is justified as this is the time range of onset of CRPS after closed treatment of DRF [26]. Unlike the pain subscales for the PRWHE, the SF-MPQ is not activity-specific, which is of necessity when evaluating the pain of an immobilized upper limb.

##### Budapest CRPS type I diagnostic criteria

A clinical assessment of CRPS presence will be conducted via use of the Budapest CRPS Type I Diagnostic Criteria [57]. These diagnostic criteria were selected over all others due to relatively higher inter-rater reliablity specificity [57]. Given that the timeframe for onset of CRPS after closed treatment of DRF has been found to be one to three months following cast removal [25], participants will be assessed upon cast removal, four weeks post removal and 12 weeks post removal. This assessment will be performed by a board certified orthopaedist with Hand Surgery training. These diagnostic criteria are presented in Table 3.

**Table 3 Tab3:** Budapest diagnostic criteria

The patient must: 1. Have continuing pain, which is disproportionate to any inciting event 2. Report at least one symptom in three of the four following categories: • Sensory: reports of hyperesthesia and/or allodynia • Vasomotor: reports of temperature asymmetry and/or skin color changes and/or skin color asymmetry • Sudomotor/edema: reports of edema and/or sweating changes and/or sweatingasymmetry • Motor/trophic: reports of decreased range of motion and/or motor dysfunction (weakness, tremor, dystonia) and/or trophic changes (hair, nail, skin) 3. Display at least one sign at time of evaluation in two or more of the following categories: • Sensory: evidence of hyperalgesia (to pinprick) and/or allodynia (to light touch and/or deep somatic pressure and/or joint movement) • Vasomotor: evidence of temperature asymmetry and/or skin color changes and/or asymmetry • Sudomotor/edema: evidence of edema and/or sweating changes and/or sweating asymmetry • Motor/trophic: evidence of decreased range of motion and/or motor dysfunction (weakness, tremor, dystonia) and/or trophic changes (hair, nail, skin) 4. Not have another diagnosis that better explains the signs and symptoms	

#### Secondary outcomes

##### Grip strength

To characterize the generalized hand strength of the sample, maximal voluntary contraction (MVC) strength of the dominant and non-dominant hands will be assessed using a Jamar™ hydraulic hand dynamometer [58]. The Jamar™ has high accuracy, good test-retest reliability [59] and was the measurement device used to collect the adult normative grip and pinch strength data by Mathiowetz et al. [60]. Three trials will be administered per hand via the positioning and verbiage recommended by the American Society of Hand Therapists [61].

##### Wrist and forearm AROM

Active wrist flexion/extension, radial/ulnar deviation and forearm pronation and supination will be measured with a goniometer (AliMed ®, Dedham, MA). The goniometer’s intra-rater reliability when taking measures of active range of motion has been established for of forearm pronation (*ICC* = .83–.86) and supination (*ICC* = .90–.93) [62] and wrist flexion (*ICC* = .96) and extension (*ICC* = .96) [63].

##### Finger edema

Circumferential measurement of the index and long finger first phalanx will be assessed as described by King [64]. In this technique, a calibrated force gauge is affixed to a Jamar™ Finger Circumference Gauge [65] and a circumferential measurement is taken when the tape is pulled with 500 g of force. This approach results in significantly less error between ratings [*F* (1,91) =15.63, *p* < 0.01] than traditional circumferential measurements, likely due to the standardized tension [64]. In general, test re-test reliability is excellent for circumferential measurements of the distal hand (*ICC* = .91) [66]. The index and long digits were chosen because Moseley used this as an outcome of a GMI intervention study and reported significant changes in digital edema. The gold standard of volumetric displacement will not be possible due to cast immobilization [67].

##### Wrist joint position sense

Wrist Joint Position Sense (JPS) testing will be used to measure conscious proprioception, a component of the sensorimotor (SM) system [68]. Karagiannopoulos et al. [69] performed wrist JPS testing in patients following closed and operative DRF and found high responsiveness in the ability of their procedure to detect change in SM function at 8 and 12 weeks following the medical intervention for DRF. The present study will use the same JPS testing protocol. The participant’s JPS is tested in two trials, with their elbow resting on a table, and eyes closed [69]. With vision occluded, the wrist is passively placed in a reference angle of 20° of extension, held for three seconds, and the participant is asked to reproduce the angle. Their final position is measured using standard goniometry procedures, and absolute values are calculated in relation to the reference angle. The statistically significant minimum detectable change (MDC) has been found to be 4.28° to 4.94° [69].

